## Abstract

**Background:**

The International Subarachnoid Aneurysm Trial (ISAT) demonstrated improved one-year clinical outcomes for patients with ruptured intracranial aneurysms treated with endovascular coiling compared to surgical clipping. Patients included in ISAT were mostly good grade subarachnoid hemorrhage (SAH) patients with small anterior circulation aneurysms. The purported superiority of coiling is commonly extrapolated to patients not studied in the original trial or to those treated using new devices not available at the time. Conversely, many patients are treated by clipping despite ISAT, because they are thought either to be better candidates for surgery, or to offer more durable protection from aneurysm recurrences. These practices have never been formally validated. Thus, for many ruptured aneurysm patients the question of which treatment modality leads to a superior clinical outcome remains unclear.

**Methods/trial design:**

ISAT II is a pragmatic, multicenter, randomized trial comparing clinical outcomes for non-ISAT patients with subarachnoid hemorrhage allocated to coiling or clipping. Inclusion criteria are broad. The primary end-point is the incidence of poor clinical outcome (defined as mRS >2) at one year, just as in ISAT. Secondary end-points include measures of treatment safety for a number of pre-specified subgroups, with efficacy end-points including the presence of a major recurrence at one year; 1,896 patients (862 each arm plus 10% losses) are required to demonstrate a significant difference between coiling and clipping, hypothesizing 23% and 30% poor clinical outcome rates, for coiling and clipping, respectively. The trial should involve at least 50 international centers, and will take approximately 12 years to complete. Analysis will be by intention-to-treat.

**Trial registration:**

ISAT II is registered at clinicaltrials.gov: NCT01668563.

## Background

To prevent re-bleeding from ruptured intracranial aneurysms, subarachnoid hemorrhage (SAH) patients are often treated by surgical clipping [1,2] or, in the last 20 years, endovascular coiling [3]. Very little randomized evidence has guided clinical decision making in neurovascular surgery since the early trials pioneered by McKissock [4] until the publication of the International Subarachnoid Aneurysm Trial (ISAT) in 2002. ISAT was a turning point in modern neurosurgical history [5]. The trial showed that for 2,143 SAH patients eligible for both surgery and endovascular coiling recruited between 1994 and 2002, randomized allocation to coiling was associated with better one-year clinical outcomes defined as survival without dependency (absolute risk reduction (ARR) of 7.4% (95% CI: 3.6 to 11.2, *P* = 0.0001). Such a ground-breaking result was bound to be received with some resistance, expressed in multiple editorials and commentaries (reviewed in [6]). However, because ISAT was a positive pragmatic trial, an appropriate interpretation of the results was that coiling should be adopted as the first-line treatment for ruptured aneurysms, at least for patients with the types of lesions included in ISAT. These were, for the great majority, small (≤10 mm) anterior circulation aneurysms [6]. Although ISAT was well designed, conducted, and reported, a single trial cannot answer all important clinical questions, and trial results were perhaps inappropriately extrapolated beyond what ISAT demonstrated [7]. Coiling has progressively replaced clipping in many centers, even for many patients that would not have been studied in ISAT [7]. Unfortunately, there is no current evidence to support coiling in the wide spectrum of non-ISAT patients and aneurysms that are currently treated endovascularly.

A recent pre-randomized study of coiling as first-intention confirmed better results for those ruptured aneurysms felt to be readily coilable; however only 62% of patients allocated to coiling were actually coiled, 38% were crossed-over to be clipped [8]. Ten years following the publication of ISAT, the optimal management of more difficult-to-coil ruptured aneurysms remains unclear.

Multiple new devices have been introduced during the last decade. This has expanded the spectrum of cases that can be treated using endovascular techniques, though no evidence is available to confirm that these patients should not be clipped instead.

Angiographic recurrences (occurring in 10% to 33% of patients [9-11]) has raised concerns that aneurysm coiling may not be as durable in the long-term as surgical clipping. ISAT patients allocated to coiling were more frequently retreated (17%) than those allocated to clipping (4%). However, clipped patients were not as rigorously followed angiographically [12,13]. Retreatments were much less frequent in the more recent Cerecyte (5.5%) and HELPS trials (3%) [10,11]. Offering a more durable protection from late re-bleeding is still a frequent reason why many neurosurgeons continue to clip ruptured aneurysms in spite of ISAT results. Furthermore, publication of the 5-year follow-up data showed that the risk of death at 5 years was significantly lower with coiling (11% versus 14%; *P* = 0.03) but the proportion of survivors that were independent did not differ between the two groups [12].

Although coiling is increasingly used in most countries, clinical practices vary tremendously, with some centers coiling as low as 20% of ruptured aneurysms, with other centers coiling upwards of 70% of ruptured aneurysms [7,14-16], depending on training, local expertise, and preferences, as well as biased data from non-randomized case series and registries [17]. Thus, for many patients the uncertainty regarding the best choice of treatment modality persists and another randomized trial is needed to offer optimal care in the presence of such uncertainty.

## Methods: Trial design

ISAT II is a randomized, multicenter, pragmatic trial comparing clinical outcomes for patients with ruptured intracranial aneurysms treated with endovascular treatment or with surgical clipping. All patients with ruptured aneurysms who are still being considered for surgical clipping in spite of ISAT results, and all those with ruptured aneurysms which were not well-represented in the original ISAT study or for which the use of new devices such as stents is contemplated, will be proposed participation in the trial. The study will be conducted in approximately 50 centers performing both surgical clipping and endovascular coiling of aneurysms, after approval from local ethics committees and with informed consent from participating patients, aiming to enroll at least 10 patients per year per center, and thus requiring approximately 10 years to recruit 1,896 patients. ISAT II will follow the principles enunciated in the Declaration of Helsinki. The complete protocol is available at http://www.clinical-care-trials.org.

### Primary hypothesis of ISAT II

Endovascular management of patients with ruptured, intradural, intracranial aneurysms suitable for both endovascular and surgical management, for whom the treating physician remains unsure whether the results of the original ISAT study apply, will lead to a decrease in the number of poor outcomes (defined as modified ranking scale (mRS) >2) from 30% to 23% at one year.

### Study endpoints

The primary end-point, as for the original ISAT study, will be the number of patients experiencing a poor clinical outcome (mRS >2) at one year post-treatment. Secondary end-points include overall mortality at one year (all causes), overall morbidity at one year (all causes), occurrence of a major (saccular) aneurysm recurrence at one year post-treatment, peri-treatment hospitalization lasting more than 15 days, discharge to a location other than home, occurrence of an intracranial hemorrhage after enrollment and for up to one year, occurrence of aneurysm re-rupture following randomization but before treatment initiation, and occurrence of failure of aneurysm occlusion using the intended treatment modality.

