### Method of allocation

After confirmation of inclusion and exclusion criteria, patients will be randomly allocated 1:1 to either surgical or endovascular management, using a centralized minimization procedure. The following factors will be balanced between groups: i) age ≥70; ii) WFNS grade >3; iii) aneurysm size ≥10 mm (using maximum aneurysm diameter on cross-sectional imaging, with the outer diameter used for partially thrombosed aneurysms); and iv) posterior circulation location. The entire randomization procedure will be performed using a web-based platform available 24 hours a day.

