### Number of patients

With target alpha 0.05 and power 90%, a sample size of 1,724 patients (862 per group, no losses) would be sufficient to demonstrate a significant difference, using estimated 23% and 30% poor clinical outcome rates for endovascular treatment (EVT) and surgical management at one year, respectively (two-sided Fisher’s exact test). We expect very few losses to follow-up (<10%), and the target sample size is 1,896 patients.

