### Planned patient follow-up

All patients will be seen in clinic at six to eight weeks, as part of routine follow-up care, followed by a telephone call at six months and another routine clinic visit at one year. These intervals will serve to determine mRS scores, and to inquire about possible aneurysm re-rupture. All patients will have non-invasive imaging (CTA or MRA) at six months to one year post-treatment to determine the presence of a major, saccular aneurysm recurrence. This follow-up is considered to be standard of care. There will be a study phone interview at five years to optimize long-term follow-up (Table 1).

**Table 1 T1:** Schedule of evaluations

**Evaluation**	**Screening**	**Pre-entry**	**Entry**	**Treatment**	**Discharge**	**6 months**	**1 year**	**5 years**
Documentation of RIA	X							
Imaging*	X						X	
Informed consent			X					
Medical history		X						
Clinical assessment		X			X		X	
Neurological exam		X			X		X	
Failure to occlude aneurysm				X				
Number of days in hospital					X			
Discharge disposition					X			
Major (saccular) aneurysm recurrence							X	
Hemorrhage during FU						X	X	X
Telephone interview						X		X

*Including catheter angiography or non-invasive imaging.

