### Planned analyses

The main statistical tests will involve comparisons between the probability of reaching the primary end-point (dependent survival or death at one year) with a surgical or endovascular management strategy. Descriptive statistics will be done on demographic variables and potential risk factors to compare the two groups at baseline. Means, standard deviations, and ranges will be presented for quantitative variables such as size of aneurysms and frequency tables for categorical variables (such as the number of patients with multiple aneurysms). Statistics will be broken down by center and by treatment arm. Comparison of the groups will be assessed through independent ANOVA (quantitative data) or Mantel-Haentzel and *χ*^2^ tests (categorical data). Assuming comparability of groups across centers, the primary outcome will be compared between groups using a Fisher’s exact test at one year.

Secondary outcomes will be compared using independent *t*-tests for quantitative variables and *χ*^2^ tests for categorical variables. The analyses of follow-up data will control for baseline data using logistic regression, ANCOVA or Cox regression multivariate methods. All tests will be interpreted with a 0.05 level of confidence.

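### Hospital stay is recorded in days but analysed only as more than 15 days or not; the collected days should be analysed alongside the split

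*Protocol article*

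**What the plan says.** In the Protocol article, Study endpoints names "peri-treatment hospitalization lasting more than 15 days" among the secondary end-points. Table 1, under Planned patient follow-up, has a row for "Number of days in hospital", marked at discharge, so the underlying quantity is collected for each patient.

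Planned analyses sets the tests by type of variable: "Secondary outcomes will be compared using independent *t*-tests for quantitative variables and *χ*^2^ tests for categorical variables". A stay classified as above 15 days or not is categorical, so it takes the chi-square route. Days in hospital is not itself listed as an end-point, so the quantitative route is not assigned to it.

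The only power statement, under Number of patients, concerns the primary end-point. The article gives no distribution of stay, no expected share above 15 days and no target difference.

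**The concern.** Under the split, a stay of 16 days counts the same as one of 90, and 3 days the same as 15. If one treatment shortens stay generally, the split uses only part of the evidence. The trial could then report no clear difference in stay when its own recorded days would show one. Even a significant result on the split says how many more patients crossed day 15, not how many days were saved or added, which is what a reader comparing two management strategies would want to know.

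This matters for one secondary comparison only.

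**Working it through.** **1. The plan's own figure.** Number of patients states: "With target alpha 0.05 and power 90%, a sample size of 1,724 patients (862 per group, no losses) would be sufficient", with rates of 23% and 30% and a "two-sided Fisher’s exact test". The usual two-proportion formula is

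n = [1.96·√(2p̄(1−p̄)) + 1.2816·√(p₁(1−p₁)+p₂(1−p₂))]² / (p₁−p₂)²,

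with p₁ = 0.30, p₂ = 0.23 and p̄ = 0.265. It gives 833.3, or 834 per arm. The continuity correction, n/4·[1+√(1+4/(n·0.07))]², gives 861.6, or 862 per arm. The stated figure is reproduced, so n = 862 per arm is used below. Allocation is 1:1 (Method of allocation).

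**2. Assumptions that are not in the article.** On some monotone scale of stay, such as log days, the coiling arm is shifted down by d standard deviations and the distribution is normal. The share of the clipping arm above 15 days is p, taken from 0.3 to 0.8. All tests are two-sided at 0.05.

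**3. Rank test on days.** θ = Φ(d/√2); null standard error σ₀ = √[(2n+1)/(12n²)] = √[1725/(12·862²)] = 0.01391; power ≈ Φ[(θ−0.5)/σ₀ − 1.96].

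Example, d = 0.135: θ = 0.5380, (0.0380)/0.01391 = 2.73, power = Φ(0.77) = 78%.

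**4. Chi-square on the split.** The coiling share is q = 1 − Φ(c + d), where c is the normal cut-point with upper tail p. Power follows from the two-proportion formula with 862 per arm.

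Example, d = 0.135: p = 0.5 gives q = 0.446 and power 61%; p = 0.8 gives q = 0.760 and power 52%.

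**5. Results over p = 0.3 to 0.8.**

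| d | Rank test on days | Chi-square at 15 days | Loss (points) |
|---|---|---|---|
| 0.05 | 17% | 11–13% | 4.5–6.4 |
| 0.10 | 53% | 31–38% | 14.6–21.3 |
| 0.135 | 78% | 52–61% | 17.3–26.5 |
| 0.15 | 86% | 61–70% | 16.0–25.4 |
| 0.20 | 98% | 85–91% | 7.1–13.3 |
| 0.25 | 99.9% | 96–98% | 1.4–3.5 |

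The loss is largest for differences that the days would show with moderate power, and small at either end. If only 20% of the clipping arm exceed 15 days, the loss at d = 0.135 is about 30 points.

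**6. Second set-up.** Fix the power of a normal-scale analysis of days at 80% (d = 0.135). The split has 61% power if 50% of stays exceed 15 days and 54% if 25% do. At 90% (d = 0.156) the figures are 73% and 66%. The losses are therefore 17 to 26 points, in line with step 5.

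**7. Does the choice of test for days matter?** Yes. Log-normal stays were simulated with log-SD 0.5 to 1.0 and 25% to 75% above 15 days, using the article's t-test on untransformed days. Its advantage over chi-square ran from about 22 points down to about −2. A rank test is unchanged by monotone transformation, so step 5 applies to skewed stays too.

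**8. Does the shape of the effect matter?** Yes. Stays were simulated as a mixture: routine, with median 10 to 14 days, and complicated, with median 25 to 30 days. Treatment changed the complicated share by 5 to 6 points. The rank test's advantage ran from about −7 to +16 points. With medians of 11 and 28 days and complicated shares of 20% and 15%, power was about 38% for the rank test and 45% for chi-square.

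**The case against.** Nothing here is contradictory. A prolonged-stay end-point is categorical, and Planned analyses gives it the matching test. It also sits naturally among secondary end-points that are all events. This stands: the point is about a better use of the data, not an inconsistency.

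A reader might infer that the 15-day cut is arbitrary because the article gives no reason for it. The documents do not support that. Methods: Trial design says a complete protocol is available elsewhere, and the reason for a secondary cut-off is something an article can leave to it. The point therefore does not rest on a missing justification; a good reason for 15 days would not restore the discarded information.

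A reader might also take 15 to 26 points as what this trial loses, or think the loss disappears only when the effect sits right at day 15. Neither holds. The range applies to shifts of 0.10 to 0.15 SD under assumed shares, and it is much smaller at other shifts. The mixture in step 8 reverses the advantage with no effect placed at the boundary.

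Nor does the article forbid a descriptive summary of days. It only fails to make days an analysed outcome.

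Finally, ranking days is not free of difficulty. An early in-hospital death produces a short stay and would rank as a good result. The split has the same defect, since such a patient counts as not exceeding 15 days, but changing to days does not cure it. A rule is needed.

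**Conclusion.** The point holds as a low-severity improvement. The article collects days in hospital and commits to analysing only a split of them, which loses information and leaves the difference in days unestimated.

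Under a general shift in stay, with the assumptions in step 2, the cost is about 15 to 26 points of power for shifts of 0.10 to 0.15 SD and falls to single figures for very small or large shifts. If treatment acts mainly on the share of complicated stays, the split may do as well or better, which is a reason to keep it rather than replace it. None of these figures is a property of the trial that can be read from the article.

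**What to change.** In Study endpoints, add days in hospital as an analysed secondary outcome beside the 15-day end-point. In Planned analyses, name a rank-based comparison for it: the Wilcoxon test, or a proportional-odds model adjusted for the four minimization factors (age, WFNS grade, aneurysm size, posterior circulation location). Report an estimated difference between arms with its 95% CI. State that the t-test on raw days is not used for this outcome, because stay is likely to be skewed.

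State one rule for in-hospital deaths so that they are not ranked as short stays, for example by ranking them worse than the longest stay. Say how the same deaths count in the 15-day share, which stays in the report.

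The cost is one additional secondary analysis and one rule for deaths. Table 1 already collects the days, so no new data, visits or patients are needed.

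### The stay-above-15-days end-point, read literally, scores death by day 15 as a favourable result, and non-home discharge may share the problem

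*Protocol article*

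**What the plan says.** Under Study endpoints, the protocol article names as separate secondary end-points "overall mortality at one year (all causes), overall morbidity at one year (all causes" and, later in the same list, "peri-treatment hospitalization lasting more than 15 days, discharge to a location other than home". Under Planned analyses, secondary outcomes that are not quantitative are compared with chi-square "tests for categorical variables", and "The analyses of follow-up data will control for baseline data using logistic regression, ANCOVA or Cox regression multivariate methods". The abstract states: "Analysis will be by intention-to-treat".

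Table 1, under Planned patient follow-up, records days in hospital and "Discharge disposition" at the discharge visit, and shows no category for death. Morbidity is not defined. No section says how a patient who dies before day 15, before discharge or before one year is classified on these three end-points.

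The primary end-point is explicit by contrast. Planned analyses describes "reaching the primary end-point (dependent survival or death at one year", so death is a failure there.

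**The concern.** Length of stay is cut short by death. A patient who dies on day 4 has not been in hospital for more than 15 days. Under intention-to-treat that patient remains in the denominator and falls into the favourable category, together with patients who recovered quickly. The end-point then mixes the best and the worst courses, and a difference between arms in early death pushes the comparison towards the arm with more deaths. Adjusting for baseline by logistic regression does not help, because the fault lies in how the outcome is coded.

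For non-home discharge the wording leaves the coding of an in-hospital death open. Coded as a non-event, it is rewarded in the same way. Excluded, the comparison is restricted to patients discharged alive, a group formed after randomisation. Coded as not home, the problem does not arise.

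At stake is a misleading secondary statement about recovery or resource use, tested at the 0.05 level.

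**Working it through.** **The plan's own figure.** The inputs are under Number of patients: 23% v 30%, two-sided alpha 0.05, power 90%.
- Uncorrected: n = [1.960·√(2·0.265·0.735) + 1.2816·√(0.30·0.70 + 0.23·0.77)]² / 0.07² = 833.3, so 834 per arm.
- With continuity correction: (833.3/4)·[1 + √(1 + 4/(833.3·0.07))]² = 861.6, so 862 per arm, as stated.
- Losses: 862 × 1.10 = 948.2, and 948 × 2 = 1,896, as stated.

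The point leaves this sample size untouched. The 862 per arm is used below.

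**Model for the stay end-point.** Let d be the proportion dead in hospital by day 15 and L the proportion with a long stay among the rest, taken as equal in both arms.
- Stand-alone rate = L(1 − d).
- Artefact between arms = L × (d_surgery − d_endovascular).
- Rate with death counted = d + L(1 − d). In-hospital deaths after day 15 are already long stays, so none is counted twice.

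**Inputs.** The article gives no value of d or L, so all values are assumptions. One pair of d is 8% v 10%. The other borrows the five-year deaths of the original ISAT from the Background, 11% coiling v 14% clipping, as an upper-end stand-in for early death. L runs from 20% to 70%.

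| d endovascular / surgery | L | Stand-alone, endovascular v surgery | Shift towards surgery | With death counted |
|---|---|---|---|---|
| 8% / 10% | 20% | 18.4% v 18.0% | 0.4 points | 26.4% v 28.0% |
| 8% / 10% | 70% | 64.4% v 63.0% | 1.4 points | 72.4% v 73.0% |
| 11% / 14% | 50% | 44.5% v 43.0% | 1.5 points | 55.5% v 57.0% |
| 11% / 14% | 70% | 62.3% v 60.2% | 2.1 points | 73.3% v 74.2% |

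In every row the stand-alone rate favours the arm with more deaths, and counting death reverses the direction.

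**Chance of a significant result for the arm with more deaths.** In the third row the standard error is √[(0.445·0.555 + 0.430·0.570)/862] = 0.0239. The shift is 0.015/0.0239 = 0.63 standard errors, so the chance is about 9%, against a nominal 2.5%.

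**Extreme case.** If the whole planned 7-point effect were early death (5% v 12%), the shift would be 0.07 × 0.20 = 1.4 to 0.07 × 0.70 = 4.9 points.

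**When it vanishes.** In the third row the two arms tie if the surgical long-stay rate among the rest is 0.445/0.86 = 51.7% instead of 50%.

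**Non-home discharge.** Let d be in-hospital death and L the non-home rate among patients discharged alive. With the same illustrative 11% / 14% and L = 50%, the three codings give 44.5% v 43.0% (non-event), 50% v 50% (excluded, equal by construction) and 55.5% v 57.0% (event). Exclusion looks neutral only because L was set equal; deaths may remove the sickest patients unevenly from the two arms.

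**Morbidity read as mRS 3-5 in all randomised patients.** Planned poor-outcome rates minus assumed one-year deaths give:
- deaths 8% v 10%: 15% v 20%, so surgery still looks worse;
- deaths 5% v 12%: 18% v 18%;
- deaths 5% v 15%: 18% v 15%, a reversal.

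Reversal therefore needs a death gap above 7 points.

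**The case against.** The strongest reply is that this is a short list of end-points in a journal article which points to a complete protocol elsewhere, and that the coding of deaths belongs there or in the analysis plan. That stands for the coding of discharge and the definition of morbidity. It does not dispose of the stay end-point, whose stated definition already classifies a day-4 death. A later rule counting that death as an event would change the end-point, not merely fill in a detail.

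A reader might infer that all three end-points count early death as a good result. The article does not support this. An in-hospital death can be read as not home, and morbidity is undefined; read as mRS 3-5 under the planning rates, it still goes against the arm with more deaths unless the death gap exceeds 7 points.

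A reader might also infer that the arm with more deaths will look better on length of stay. That needs a real gap in deaths by day 15 and similar long-stay rates among the rest. The article hypothesises a difference in mRS >2 and none in early mortality, and an arm with more deaths may well have more long stays.

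Two further points stand. All-cause mortality is reported alongside these end-points, so deaths by arm will be visible. Scoring a day-4 death as a long stay would misstate resource use if only the composite were shown, so the components have to be tabulated too.

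**Conclusion.** The point holds for the stay end-point: read literally under intention-to-treat, it scores death by day 15 as a favourable non-event. It holds conditionally for non-home discharge, if in-hospital deaths are coded as non-events or excluded. For morbidity only the missing definition remains.

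On assumed early-death gaps of 2 to 3 points, L of 20% to 70% and equal L in both arms, the artefact is modest, but it can reverse the apparent direction. None of these rates comes from the article as an early-death or long-stay rate. The trial's main conclusion is not at risk.

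**What to change.** Analyse two composites in all randomised patients: in-hospital death or a stay above 15 days, and in-hospital death or non-home discharge. Beside each, tabulate death and the separate component by arm, so that resource use can still be read.

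Keep morbidity as its own end-point, define it, and show mRS 0-2, 3-5 and 6 by arm. Do not replace it with death or mRS 3-5, which repeats the primary end-point.

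The cost is a change of wording, made by amendment because the article reports that recruitment has begun. Length of stay, disposition, mRS and mortality are already planned data; it should be confirmed that the disposition field can record an in-hospital death. The small downside is that the composites mix death with softer outcomes.
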